**Table 2. Proposed Dose Levels**

| Dose Level   | 1    | 2    | 3    |  |  |  |  |  |  |  |  |
|--------------|------|------|------|--|--|--|--|--|--|--|--|
| Dose (mg/kg) | 0.16 | 0.32 | 0.53 |  |  |  |  |  |  |  |  |

Throughout all parts of the study, ABBV-467 will be administered with an abbreviated dose ramp-up, in which 50% of the target dose will be administered on Cycle 1 Day 1 (C1D1), and full target dose thereafter (weekly until disease progression, unacceptable toxicity, or withdrawal of consent).

For each dose level, the second subject will not be dosed until at least 48 hours have elapsed since the initial dose for the first subject at that dose level.

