### Part A and Part C

Subjects with R/R MM (Part A) will receive escalating doses of ABBV-467 as described above. Once a pharmacologically and/or clinically active and tolerable dose is identified based on review of totality of safety, efficacy, PK and PD data, this dose will be used to commence dose escalation in R/R AML (Part C), where provisional dose de-escalation will also be permitted.

In order to be considered DLT evaluable, a subject must either:

1. receive each of planned doses *and* at least 80% of the total planned dose of ABBV-467 for Cycle 1; or
2. experience a DLT after receipt of at least one dose of ABBV-467 during the DLT evaluation period.

Selection of doses used in the study, including the optimal biological dose (OBD) and RP2D, can be found in Section 4.2.

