### Hepatic Laboratory Abnormalities

Subjects should be monitored closely for hepatic-related laboratory abnormalities and AEs. In instances of new observations of hepatic laboratory abnormalities (i.e., ALT and/or AST  $> 1- < 3 \times \text{ULN}$  and/or total bilirubin  $< 2 \times \text{ULN}$ ), clinical chemistries should be re-tested within 48 to 72 hours.

An algorithm for monitoring and management of drug-induced liver injury in subjects with normal or elevated baseline ALT and/or AST (defined as the average of 2 screening measurements) is available in [Appendix H](#) and should be used for study drug-related toxicity management. Guidelines should be followed for all subjects regardless of baseline liver function laboratory values. Hy's law is defined as ALT/AST and bilirubin in the normal reference range prior to study drug dosing, with subsequent development of ALT or AST  $\geq 3 \times \text{ULN}$  along with total bilirubin  $> 2 \times \text{ULN}$ , without findings of cholestasis

(elevated serum ALP) and with no alternative explanation. Any suspected cases of Hy's Law will require clinical review and confirmation.

Any increase in ALT and/or AST that is  $\geq 3 \times \text{ULN}$  but  $< 5 \times \text{ULN}$ , the dose will be held until the toxicity resolves to Grade 1 or lower, or to baseline if the toxicity was  $> \text{Grade 1}$  at the time of study entry. Upon toxicity resolution, the subject may restart study drug at a dose that is at least 33% lower than the previous dose. For ALT and/or AST increase  $\geq 5 \times \text{ULN}$  study drug may be restarted only if another etiology is identified and liver enzymes return to baseline.

In the event of hepatic abnormalities, documentation which captures relevant clinical signs and symptoms should be completed by the site in the source records and corresponding eCRF(s). In addition, for hepatic abnormalities, this should include imaging as clinically indicated (e.g., abdominal ultrasound, endoscopic retrograde cholangiopancreatography) to exclude alternative etiologies of liver injury (with full reports made available).

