## 6.3 Dose-Limiting Toxicity

---

Dose-limiting toxicity for dose escalation purposes will be determined on events that occur during the first 28-day cycle.

Any AE of Grade 3 or higher will be considered a DLT, unless toxicity can solely be attributed to the underlying disease, with the following clarifications. Adverse events of any grade resulting in discontinuation of study drug will be considered a DLT. Missing any dose as a result of toxicity unexplained by the underlying disease will also be considered a DLT.

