### Hematologic DLTs (regardless of attribution)

For subjects with MM, hematologic DLTs are defined as:

- Grade 4 neutropenia lasting for > 5 days.
- Grade 4 anemia unexplained by underlying disease.
- Febrile neutropenia defined as ANC < 1000/mm^3 with a fever ≥ 38.3°C or ≥ 38°C for 1 hour.
- Grade 4 thrombocytopenia.
- Grade 3 thrombocytopenia associated with clinically significant bleeding.

For subjects with AML, hematologic DLTs are as follows:

- ANC < 500/mm^3 and/or platelet < 25,000/mm^3 at either/both of the following time points (and only in the setting of a bone marrow response assessment showing < 5% blast count):
  - Day 42 from first dose of ABBV-467
  - 14 days beyond cessation of ABBV-467

For AML subjects with evidence of myelosuppression at 28 days, the DLT period will be 42 days or 14 days after bone marrow biopsy showing < 5% blast count (whichever is later). NOTE: In any instance in which bone marrow response assessment is either undocumented, or consistent with  $\geq$  5% blast count, cytopenias should be attributed to persistence of AML, rather than study drug (and therefore should not be considered DLT).

The DLT evaluation period will be 28 days irrespective of dose frequency (should other treatment schedules be explored).

Subjects who do not complete all of the scheduled doses of ABBV-467 or who do not receive at least 80% of the planned total dose during the DLT evaluation period, due to reasons other than occurrence of DLT(s) will be considered non-evaluable for DLT, and may be replaced to ensure the accrual of the minimum number of subjects to adequately assess tolerability (other subjects who withdraw consent or refuse further follow-up will be replaced). All safety information including information on AEs, etc., observed in subjects who are excluded from DLT evaluation will be taken into consideration to determine the next dose level.

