| ≥ 3 -
< 5 × ULN                | Normal
(TBL
< 2 × baseline in
subjects with
Gilbert
syndrome) | Absent                | 
 
Hold treatment
 
Monitor LFTs every 3 - 5 days
 
Restart study drug at ≥ 33% dose reduction if LFTs return to baseline or < 3 × ULN (permanently discontinue treatment if LFTs become abnormal with treatment at reduced dose)
 
 |                                                                                                                                                                                                                                                                                                                                                                                    |
| ≥ 3 -
< 5 × ULN                | > 2 × ULN and/or
INR > 2.0                                                | Absent or
present  | 
 
Permanently discontinue treatment
 
                                                                                                                                                                                                               | 
 
Consider inpatient evaluation
 
                                                                                                                                                                                                                                                                                                    |
| ≥ 5 × ULN                         | Any                                                                          | Absent or
present  | 
 
Permanently discontinue treatment unless another etiology is identified and liver enzymes return to baseline
 
                                                                                                                                    | 
 
Monitor LFTs every 1 - 2 days
 
Consider hepatology consultation
 
                                                                                                                                                                                                                                                          |

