|                                                                                                               |                                                                                                                                                                                                                                |                                                                                                                                                  |
|---------------------------------------------------------------------------------------------------------------|--------------------------------------------------------------------------------------------------------------------------------------------------------------------------------------------------------------------------------|--------------------------------------------------------------------------------------------------------------------------------------------------|
| [figure not shown] INTERVIEW            | 
 
Adverse event assessment
 
                                                                                                                                                     | 
 
Prior/concomitant medications
 
                                                                  |
| [figure not shown] LOCAL LABS AND EXAMS | 
 
Vital signs
 
                                                                                                                                                                  | 
 
TLS prophylaxis
 
TLS chemistry panel (Day 2 only)
 
                                      |
| [figure not shown] CENTRAL LABS         | 
 
Hematology/chemistry
 
Triplicate ECG (Day 2 only)
 
Creatine phosphokinase and troponin (Days 2 & 3 only)
 
Blood PK samples (Days 2 & 3 only)
 
 | 
 
Urine PK samples (Days 2 & 3 only)
 
Peripheral blood biomarker sample (Day 2 only)
 
 |

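### A drug toxicity that is not itself a DLT but cuts the Cycle 1 dose below 80% of plan removes the subject from the BOIN count, although the same toxicity counts as a DLT if it causes one missed dose

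*Protocol*

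**What the plan says.** Section 6.3 makes most Grade 3 or higher events in the first 28-day cycle DLTs. It then adds two rules that apply whatever the grade: "Adverse events of any grade resulting in discontinuation of study drug will be considered a DLT", and "Missing any dose as a result of toxicity unexplained by the underlying disease will also be considered a DLT". Dose reduction for toxicity is not on the list. Grade 3 mucositis, nausea, vomiting and diarrhea are exempt unless they need parenteral nutrition, tube feeding or a hospital stay beyond 72 hours.

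Evaluability is defined twice. Section 4.1 (Part A and Part C) requires every planned dose and "at least 80% of the total planned dose of ABBV-467 for Cycle 1", or else a DLT. Section 6.3 says that subjects are non-evaluable and may be replaced if they miss scheduled doses or if they "do not receive at least 80% of the planned total dose during the DLT evaluation period, due to reasons other than occurrence of DLT(s". It adds that safety information from excluded subjects will be considered when the next dose level is chosen.

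Dosing is ramped up: "50% of the target dose will be administered on Cycle 1 Day 1 (C1D1), and full target dose thereafter". For ALT/AST of 3 to <5 × ULN, Section 6.2 (Hepatic Laboratory Abnormalities) holds the drug until resolution, after which "the subject may restart study drug at a dose that is at least 33% lower than the previous dose"; Appendix H agrees ("Restart study drug at ≥ 33% dose reduction if LFTs return to baseline"). For other drug-attributed Grade 3/4 toxicity, Section 6.2 allows a restart at 75% of the starting dose. Neither rule is barred in Cycle 1. Appendix D schedules chemistry on Cycle 1 Days 2 to 5.

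**The concern.** An 80% dose rule normally sets aside subjects who were under-exposed for reasons unrelated to the drug, because they say little about tolerability. Here the exemption is for shortfalls caused by a DLT, not for shortfalls caused by toxicity. A subject whose doses were reduced because the drug was not tolerated, without meeting a DLT criterion, is therefore treated like one who missed visits for logistical reasons. Since Section 4.1 already requires every planned dose, the 80% limb adds something only when doses are reduced or incomplete, so this case lies squarely within its reach.

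Section 6.3 takes the opposite line on missed doses and discontinuations, where toxicity of any grade counts. At stake is the DLT count that drives escalation, de-escalation and elimination in a first-in-human trial. The effect, where it occurs, is to drop drug-intolerant subjects.

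**Working it through.** **The plan's own figures.** With target 0.25 and limits 0.6 × 0.25 = 0.15 and 1.4 × 0.25 = 0.35 (Section 4.1):

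- escalation boundary = ln(0.85/0.75) / ln[0.25 × 0.85 / (0.15 × 0.75)] = 0.1968
- de-escalation boundary = ln(0.75/0.65) / ln[0.35 × 0.75 / (0.25 × 0.65)] = 0.2984

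These match the stated 0.197 and 0.298, and the escalate and de-escalate rows of Table 1 follow from them. The boundaries are sound; the question is which subjects feed them.

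**Cycle 1 dose.** In units of the target dose, the plan is 0.5 + 1 + 1 + 1 = 3.5, and 80% of that is 2.8. Cuts below are taken from the target dose, the reading that leaves the most drug.

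| Course | Doses given | Total | % of plan | Status |
|---|---|---|---|---|
| Day 22 missed for toxicity | 0.5, 1, 1, 0 | 2.50 | 71.4 | DLT |
| ALT/AST 3 to <5 × ULN after Day 1, resolved by Day 8, 33% cut | 0.5, 0.67, 0.67, 0.67 | 2.51 | 71.7 | Non-evaluable |
| Exempt Grade 3 GI event after Day 1, resolved by Day 8, restart at 75% | 0.5, 0.75, 0.75, 0.75 | 2.75 | 78.6 | Non-evaluable |
| 33% cut from Day 15 | 0.5, 1, 0.67, 0.67 | 2.84 | 81.1 | Evaluable, no DLT |
| 25% cut from Day 15 | 0.5, 1, 0.75, 0.75 | 3.00 | 85.7 | Evaluable, no DLT |
| 40% cut from Day 15 | 0.5, 1, 0.6, 0.6 | 2.70 | 77.1 | Non-evaluable |

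The ALT/AST event is Grade 2 if baseline was normal (Appendix H), so it is not a DLT by grade. Rows 1 and 2 receive almost the same dose and are classified differently.

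**Effect on Table 1.** Three evaluable subjects without a DLT plus one subject excluded this way read as 0/3, which is escalate; counted, the result is 1/4, which is stay. At dose levels 1 and 2, where two evaluable subjects suffice, 0/2 is escalate; counted, 1/3 is de-escalate.

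**Illustration of size.** The protocol gives no frequency, so these rates are assumptions. Let p be the DLT rate under the current text and r the share of subjects excluded by this route, with p + r = 0.25. The rate seen after replacement is p/(1 − r), and the chance of 0/3 is [1 − p/(1 − r)]³.

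| r | Rate seen | P(0/3), excluded | P(0/3), counted |
|---|---|---|---|
| 0.05 | 0.20/0.95 = 0.211 | 0.492 | 0.75³ = 0.422 |
| 0.10 | 0.15/0.90 = 0.167 | 0.579 | 0.422 |
| 0.15 | 0.10/0.85 = 0.118 | 0.687 | 0.422 |

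Holding p at 0.20 instead, counting these events lowers P(0/3) from 0.492, 0.471 and 0.447 to 0.422, 0.343 and 0.275 for the same r. These are chances of a Table 1 recommendation to escalate, not of escalation itself.

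**The case against.** **The route is narrow.** The toxicity must not be a DLT, must appear after the Day 1 half dose and must clear before Day 8. If it does not clear, a dose is missed and the subject is already a DLT. After Day 8, a minimum hepatic cut leaves 81.1% and only a deeper one excludes. This stands, and it makes the larger values of r above implausible. Grade 2 pancreatitis carries the same 33% cut but is a weak example: the protocol's grading defines no Grade 1, so in effect it must resolve completely within a week.

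**All data are weighed.** Section 4.1 says an escalation recommendation is decided in light of all available information and allows an intermediate dose; Section 6.3 requires excluded subjects' safety data to be considered. A reader might infer that 0/3 compels escalation, and the protocol does not say so. This stands as mitigation, but it is discretionary: it puts no one into the Table 1 count and cannot trigger elimination.

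**The DLT rate is not too low on the protocol's own definition.** A reader might infer that replacement biases the protocol-defined rate downwards. It does not: p/(1 − r) exceeds p. The count is low only if these events ought to be DLTs. The reason to think so is the protocol's own missed-dose rule.

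**A more dramatic contrast is available.** If the 33% is taken literally from the previous dose, here the half dose, the total is 0.5 + 3 × 0.335 = 1.505, or 43.0% of plan. The protocol does not state the base of the cut in Cycle 1, so 43% is one reading only and the point does not rest on it.

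**Counting these events over-calls.** Reversible low-grade toxicity would become a DLT, and the same ALT rise after Day 8 (81.1%) would not. The second part is true of any 80% cut-off. The first fails as an argument for the present text, because the missed-dose rule already makes such low-grade events DLTs.

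**Conclusion.** The point holds as a gap in the evaluability rule. Below 80% of plan, Sections 4.1 and 6.3 separate DLT from non-DLT reasons when they should separate toxicity from other reasons. As a result, some drug-intolerant subjects can be replaced while others with nearly the same dose (71.4% against 71.7%) are DLTs. One such subject can change a Table 1 recommendation from stay to escalate, or from de-escalate to escalate in the first two dose levels.

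The overall effect cannot be sized from the protocol. It depends on how often a sub-DLT toxicity clears within a week or leads to a deep later cut, which is unknown and probably uncommon, and on how far the all-data review compensates. The conclusion also assumes that toxicity-driven reductions should be treated as the protocol treats toxicity-driven missed doses. It merits correction because the rule operates during escalation and the omission favours escalating.

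**What to change.** In Section 6.3, add that any toxicity unexplained by the underlying disease that brings the Cycle 1 total below 80% of the planned dose is a DLT. In Sections 6.3 and 4.1, limit non-evaluability and replacement to shortfalls for reasons other than toxicity. State also whether a Cycle 1 reduction is taken from the Day 1 half dose or from the target dose.

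This is protocol wording only, with no new visits, assessments or BOIN boundaries. Some Grade 2 events become DLTs, so escalation is slightly more cautious; fewer subjects need replacing.

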## 7 STATISTICAL METHODS & DETERMINATION OF SAMPLE SIZE

### 7.1 Statistical and Analytical Plans

---

Complete and specific details of the statistical analysis will be described and fully documented in the Statistical Analysis Plan (SAP). The SAP will be finalized prior to the database lock. The statistical analyses will be performed using SAS (SAS Institute Inc., Cary, North Carolina, USA).

### 7.2 Definition for Analysis Populations

---

Efficacy and safety analyses will be performed on the all-treated population which comprises all subjects who receive at least 1 dose of study drug. The PK population is defined as subjects who received at least 1 dose of study drug and have at least 1 valid post-baseline PK data; PK analyses will be based on the PK population.

Details on the analysis population definitions will be provided in the SAP.

### 7.3 Statistical Analyses for Efficacy

---

Efficacy analysis will be performed separately for subjects with R/R MM and R/R AML.

Efficacy for R/R MM subjects will include analyses of ORR (PR + VGPR + CR + sCR), DOR, and CBR.

Efficacy for R/R AML subjects will include analyses of CRc rate (CR + CRi), CRh, ORR (CRc + PR), and DOR.

Exploratory efficacy analysis includes overall survival (OS) for both R/R MM and R/R AML.

For Parts A and C, efficacy data will be listed for each dose level.

For Parts B and D, efficacy analyses will be performed by cohort for the all-treated population. For binary endpoints (such as ORR, CBR, CRc, CRh), the estimated proportion and the associated 2-sided 90% Clopper-Pearson (exact) confidence intervals (CIs) will be provided for each cohort. DOR will be defined as the time between date of first response and the first occurrence of progression or death from any cause, whichever occurs first. Only responders will be included in the analysis of DOR. DOR for subjects without DOR events at the time of analysis will be censored at the date of last disease assessment. If a subject receives a new anti-cancer therapy, DOR will be censored at the date of last disease assessment prior to the start of the new therapy. DOR will be summarized using the Kaplan-Meier method. The median DOR and its associated 2-sided 90% CIs will be provided for each cohort. For R/R MM subjects, DOR will be analyzed among subjects who achieved PR, VGPR, CR or sCR. For R/R AML subjects, DOR will be analyzed among subjects who achieved CRc or PR. OS will be defined as the time from the date of the first dose of study treatment to the date of death. For subjects who are not deceased, the data will be censored at the last known alive date. OS will be summarized using the Kaplan-Meier method. The median OS and its associated 2-sided 90% CIs will be provided.

Additional details on the efficacy analyses are provided in the SAP.

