#### Multiple Myeloma

For MM, efficacy will be evaluated per adapted International Myeloma Working Group (IMWG) criteria:

- Overall response rate (ORR), defined as partial response (PR) + very good partial response (VGPR) + complete remission (CR) + stringent complete response (sCR).
- Clinical benefit rate (CBR), defined as minimal response (MR) + PR + VGPR + CR + sCR.

Duration of response (DOR), defined as the time between date of first response and the first occurrence of progression or death from any cause, whichever occurs first.

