## Acute Myeloid Leukemia

For AML, efficacy will be evaluated per adapted International Working Group (IWG) and European Leukemia Net (ELN) criteria:

- Composite complete remission (CRc), comprised of CR + CR with incomplete blood count recovery (CRi).
- CR + CR with partial hematologic recovery (CRh).
- ORR, comprised of CRc + PR.
- DOR, as defined above.

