### Acute Myeloid Leukemia Assessments

Assessments of AML disease status by the modified International Working Group (IWG) criteria (see Section 7.4) will be performed at the visits indicated in Section 2.

All AML subjects will have response assessment according to the modified IWG criteria for AML. Progressive disease is defined per European LeukemiaNet recommendations. If additional treatments are needed to optimize subjects' medical care, they can be performed following institutional standards and procedures. Subject's disease assessment is based on the most recent physical examination, bone

marrow results and recent hematology values. For subjects who require a delay in next cycle of study treatment for blood count recovery after a bone marrow evaluation, hematology values for up to 2 weeks or pre-dose labs from Day 1 of the next cycle can be used to determine the IWG response.

All AML subjects who completed at least 1 cycle of study treatment will be assessed by the investigators using the modified IWG criteria for AML as described in Section 7.4. Subjects who have discontinued study treatment prior to completion of Cycle 1 will be deemed non-evaluable for response assessment. In addition to the response assessment using the above response criteria, each subject will also be evaluated for complete response with partial hematologic recovery (CRh) based on the hematologic parameters.

Bone marrow aspirate and biopsy should be completed as outlined in Section 2. Bone marrow aspirates and biopsies performed as standard of care throughout the study should also be captured on an eCRF.

A bone marrow aspirate and biopsy must be performed for all subjects during screening to collect mandatory samples for disease and biomarker assessments. Bone marrow aspirate and biopsy will also be collected anytime that progressive disease is suspected.

Bone marrow biopsy materials (i.e., block or slides) are to be submitted from screening and final visits, and aspirate is to be provided from screening, C2D1, Day 1 of every 3 Cycles thereafter (i.e., C5D1, C8D1, C11D1, etc.), and the Final Visit. Additionally, should an aspirate be performed at any time to confirm a CR or when one is suspected, then an aliquot for biomarker studies should be provided.

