| Morphologic Leukemia-Free State (MLFS)                      | Less than 5% blasts in an aspirate sample with marrow spicules and with a count of at least 200 nucleated cells.                                                                                                                                                                                                                                                                                                                                                                                                                                                                                                                                                                                                                                     |
| Resistant Disease (RD)                                      | Failure to achieve CR, CRi, PR; in subjects surviving at least 7 days following completion of Cycle 1 treatment, with evidence of persistent leukemia by blood and/or bone marrow examination. Study treatment may continue beyond RD if subject is continuing to derive clinical benefit, in opinion of treating investigator.                                                                                                                                                                                                                                                                                                                                                                                                                      |
| Morphologic Relapse                                         | Reappearance of $\geq$ 5% blasts post CR in peripheral blood or bone marrow                                                                                                                                                                                                                                                                                                                                                                                                                                                                                                                                                                                                                                                                          |

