| Progressive Disease                                         | Progressive disease per ELN Criteria c (ANY of the following): 
 
50% increase in marrow blasts over baseline (a minimum 15% point increase is required in cases with < 30% blasts at baseline; or persistent marrow blast percentage of > 70% over at least 3 months; without at least a 100% improvement in ANC to an absolute level (<math>> 0.5 \times 10^9</math>/L [500/mL], and/or platelet count to <math>> 50 \times 10^9</math>/L [50,000/mL] non transfused);
 
50% increase in peripheral blasts (WBC <math>\times</math> % blasts) to <math>> 25 \times 10^9</math>/L (<math>> 25,000</math>/<math>\mu</math>L);
 
New extramedullary disease
 
 |

ANC = absolute neutrophil count; BM = bone marrow; CR = complete remission; CRc = composite CR; CRh = CR with partial hematologic recovery; CRi = CR with incomplete blood count recovery; CRp = CR with incomplete platelet recovery; ELN = European LeukemiaNet; IWG = International Working Group; MLFS = morphologic leukemia-free state; OS = overall survival; PR = partial remission; RD = resistant disease

a. CRp should be categorized as CRi.

- b. In addition to the other response categories, subjects should be classified at each disease assessment for presence of CRh (independent of best response). Subjects could, therefore, be classified as achieving CRh as well as other response categories listed above at any given assessment.
- c. Progressive disease as defined by ELN criteria.

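### In AML, duration of response counts progression or death but not morphologic relapse, so remissions lost below the progression thresholds are counted late or censored and the Kaplan-Meier DOR is biased upward

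*Protocol*

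**What the plan says.** Section 3.2 gives the DOR definition under multiple myeloma: "defined as the time between date of first response and the first occurrence of progression or death from any cause, whichever occurs first". The AML list in the same section says only "DOR, as defined above". Section 7.3 repeats one definition for both diseases: "DOR will be defined as the time between date of first response and the first occurrence of progression or death from any cause".

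The AML analysis set is wider than complete remission: "For R/R AML subjects, DOR will be analyzed among subjects who achieved CRc or PR", where CRc is CR plus CRi. A responder without an event is censored at the last disease assessment. For new treatment the rule is "If a subject receives a new anti-cancer therapy, DOR will be censored at the date of last disease assessment prior to" the start of that therapy. DOR is summarised by cohort as a Kaplan-Meier median with a 2-sided 90% confidence interval.

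The AML criteria in Operations Manual Section 7.4 have two separate rows:

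- **Morphologic relapse:** at least 5% "blasts post CR in peripheral blood or bone marrow".
- **Progressive disease**, any of: "50% increase in marrow blasts over baseline", with a minimum rise of 15 percentage points if baseline is below 30%; marrow blasts staying above 70% for 3 months or longer; a 50% rise in peripheral blasts to more than 25 x 10^9/L; or new disease outside the marrow.

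Operations Manual Section 3.16 adds: "Progressive disease is defined per European LeukemiaNet recommendations". It also calls for a response assessment whenever relapse is suspected, so relapse is looked for. The post-treatment note in Operations Manual Section 2.2 collects disease status until progressive disease or new anticancer therapy and does not mention relapse.

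**The concern.** In myeloma, progression is measured from the lowest confirmed value on study, so it captures loss of response. In AML, under these criteria, the 50% marrow criterion is measured from the pre-treatment value, and loss of a complete remission has its own, much lower threshold under another name. A definition written for the first disease and carried into the second leaves that loss out.

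A CR or CRi that ends in relapse below the progression thresholds is not an event when remission is lost. Three things can then happen under the stated rules:

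- The subject later meets progression or dies, and the event is counted late.
- The subject starts new therapy and is censored. This censoring is informative, because relapse is a natural reason to change therapy.
- The data are cut first, and the subject is censored at the last assessment, which may fall after the relapse.

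Each adds time out of remission to DOR or removes a failure from it. The reported median would describe something longer than the duration of remission.

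**Working it through.** The protocol gives no DOR figure (no assumed median or event count), so there is nothing to reproduce. The check has two parts.

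**1. Distance between the two thresholds.** Marrow blasts needed for the 50%-increase criterion are 1.5 x baseline, or baseline + 15 points if that is larger and baseline is below 30%. Relapse needs 5%.

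| Baseline | Calculation | Needed for this criterion |
|---|---|---|
| 10% | max(15, 25) | 25% |
| 20% | max(30, 35) | 35% |
| 30% | 1.5 x 30 | 45% |
| 40% | 1.5 x 40 | 60% |
| 60% | 1.5 x 60 | 90% |
| above 66.7% | 100 / 1.5 = 66.7 | cannot be reached |

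The last row concerns this criterion only. Persistent blasts above 70%, peripheral blasts and new extramedullary disease remain possible routes to progression.

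**2. Effect on the median, illustrated.** Every input is an assumption, because the protocol supplies none:

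- exponential times, with median time to relapse 4 months and median time to death in remission 24 months;
- a share q of relapses that already meet progression when they occur;
- of the remaining relapses, a share c re-treated and censored at relapse, with c from 0 to 0.6;
- for the rest, a lag with median 2 months from relapse to progression or death.

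With relapse counted as an event, the hazard is ln2/4 + ln2/24 = ln2 x 7/24, so the median is 24/7 = 3.43 months. Simulating 100,000 subjects per setting under the protocol's rule gives:

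| q | Median, c = 0 | c = 0.3 | c = 0.6 | Ratio to 3.43 |
|---|---|---|---|---|
| 0.1 | 5.80 | 6.51 | 7.75 | 1.7 to 2.3 |
| 0.3 | 5.27 | 5.70 | 6.45 | 1.5 to 1.9 |
| 0.5 | 4.73 | 4.96 | 5.33 | 1.4 to 1.6 |
| 0.7 | 4.20 | 4.25 | 4.42 | 1.2 to 1.3 |
| 1.0 | 3.40 | 3.43 | 3.44 | 1.0 |

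The inflation disappears only when every relapse already meets progression. The simulation assumes loss of remission is seen when it occurs and ignores the spacing of marrow assessments.

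**The case against.** **The word progression might be meant to include relapse.** Section 5.5 refers to progressive disease in AML per IWG and ELN criteria together, Section 3.2 assesses efficacy under both, and Section 7.3 leaves further detail to the SAP. This would make the text ambiguous rather than wrong. It does not carry far. Section 3.16 of the Operations Manual ties progressive disease to ELN, and Section 7.4 sets relapse in a separate row. Section 7.3 itself states the event, the censoring rules and the analysis set, so a SAP that added relapse would be changing a definition the protocol has fixed.

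**The size is unknown and easily exaggerated.** This stands. A reader might infer that most losses of remission go uncounted, but the documents give no distribution of blasts at relapse. With baseline blasts assumed uniform from 20% to 90%, and relapse blasts uniform from 5% up to 30%, 60% or 90%, the share meeting the 50%-increase criterion is 0%, 7% or 20%. Those are assumed distributions, and they set aside the other progression criteria.

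A reader might also multiply the median by 1/(1 - f), where f is the share of losses that are sub-threshold relapses. That treats each one as permanently censored, whereas an untreated relapse becomes an event later through progression or death. In the illustration relapses are (1/4)/(7/24) = 6/7 of losses. At q = 0.1, f = 0.9 x 6/7 = 0.77 and the multiplier is 4.4, against a simulated 1.7 to 2.3.

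**The consequences are limited.** This also stands. The study is first-in-human, efficacy is secondary, and there is no formal test. Part C efficacy is only listed. The AML Kaplan-Meier analysis concerns Part D, with 20 response-evaluable subjects and at most 24 enrolled. At the 25% rate in Table 5 there are 5 responders, so the median will be imprecise under either definition. With so few, however, one misclassified relapse is 1/5 = 20% of that group.

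**Conclusion.** The point holds as a defect in the stated definition. For AML subjects in CR or CRi, loss of remission by morphologic relapse is not a DOR event unless it also meets progressive disease, and the resulting delay or informative censoring can only lengthen the estimate. The direction follows from the text and needs no assumption beyond some relapses falling below the progression thresholds.

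The size does not follow from the text. Across the settings with q from 0.1 to 0.7 the median is inflated about 1.2 to 2.3 times, and this rests on the assumed relapse, death and lag times and on the two unknown shares. The documents support neither a claim that most losses are missed nor a larger multiple.

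The relapse row refers to CR, so the point does not extend to loss of a PR. It should be corrected before AML DOR is analysed. It does not bear on safety, dose selection, sample size or error rates.

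**What to change.** In Sections 3.2 and 7.3, give AML its own definition: DOR runs from first response to the earliest of morphologic relapse after CR or CRi (Operations Manual Section 7.4), progressive disease, or death from any cause. State explicitly that relapse applies after CRi as well as CR, since the table row says only CR, and that loss of a PR is counted through progressive disease or death. Add relapse to the disease-status note in Operations Manual Section 2.2 so that it is recorded during post-treatment follow-up.

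The cost is a few sentences. Relapse is already assessed when suspected, so no new on-treatment visit or procedure is needed. Reported DOR will be shorter than under the present wording.
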